**Figure 2 F2:**
[figure not shown]
Management pathway (a priori defined management pathway based on the presence or absence (or no CT done) of bronchiectasis and on the amount of secretions and colour of secretions which are part of the bronchitis score). BAL, bronchoalveolar lavage; PO, per oral.

### Sample size

Our target sample size is based on finding a difference between groups of at least the minimal clinically important difference (MCID) of PedsQL 4.0 (primary outcome). With MCID of the total parent proxy of 4.5 (SD 8.25),^40^ for a study power of 90% (α=0.05), data from 48 children per group (total 96) are required. To account for a dropout of 15%, we will enrol a total of 114 children (57 children per group). For the secondary outcome of ‘change in management’, the effect size is conservatively estimated based on pilot data of a random selection of 20 FBs and using the a priori definitions aforementioned. Our pilot work found that FB led to a change in management in 14 of the 20 children (70%). The sample size of 114 provides 95% power (α=0.05) for this outcome (taking into account 15% loss).

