### Randomisation and allocation

Randomisation is stratified by as follows: (a) indication for FB (chronic cough or other indications (recurrent stridor, recurrent wheeze, haemoptysis, recurrent pneumonia, persistent radiographic changes, suspicion of foreign body, unexplained dyspnoea and others) and (b) age (≤2 or >2 years). The computer-generated permuted block (block size 4–6) randomisation allocation sequence (1:1 ratio) was prepared by an independent person not involved in the study. After informed consent, children are randomised to one of the two arms: (1) intervention group where the FB occurs early or (2) control group where the FB occurs within the normal waiting time. Parents of participants will not be informed of the usual wait times; thus, they are unaware of whether they are in early or ‘usual-wait’ group and hence will remain blinded. Blinding the physician is not possible.

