### Data management and statistical analyses and reporting

Essential study documentation and management of all study files are in accordance with good clinical practice guidelines. Further information about data management are provided in online supplemental file 1.

Data will be reported in accordance with Consolidated Standards of Reporting Trials, and ‘intention to treat’ (ITT) analyses will be used. For PedsQL 4.0, data will not be imputed, and ITT will consist of ‘available cases’. Based on our previous RCT,^38^ the change in PedQL 4.0 is expected to be normally distributed. The difference (with 95% CI) between groups of the change in QoL will be calculated using unpaired Student’s t-test. If the groups are imbalanced at baseline, regression analyses (adjusting for baseline factors) will be used instead. For the secondary outcomes of DASS21, STAI and PAC-QoL (including cough severity scores), the same method as per PedsQL 4.0 will be used. For the outcome of ‘change in management’, χ^2^ will be used to analyse the difference in the proportion between groups, presented as odds ratio (95% CI). Likert scales regarding opinions towards benefit of FB (parent and doctor perspective) will be reported as mean (SD) or median (25th–75th percentile), based on data distribution.

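### The stated inputs for the primary outcome do not give 90% power with 48 children per group: at a 4.5-point difference and SD 8.25 the power is about 75%.

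*Protocol article*

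**What the plan says.** The Sample size section of the protocol article aims the trial at "finding a difference between groups of at least the minimal clinically important difference (MCID) of PedsQL 4.0 (primary outcome". The inputs follow: "With MCID of the total parent proxy of 4.5 (SD 8.25", and then "for a study power of 90% (α=0.05), data from 48 children per group (total 96) are required". An allowance of 15% for dropout raises this to 57 per group, 114 in all.

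The section on data management and statistical analyses fixes the test: "The difference (with 95% CI) between groups of the change in QoL will be calculated using unpaired" Student's t-test. It analyses available cases without imputing PedsQL 4.0 data. Regression adjusting for baseline factors replaces the t-test only if the groups turn out imbalanced at baseline. The section on randomisation gives equal allocation.

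The article does not say whether 8.25 is the SD of the T2 minus T1 change or of a score at one visit. It gives no T1–T2 correlation and mentions no one-sided test.

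**The concern.** Difference, SD, alpha, power and group size are all printed, so any four of them determine the fifth. A standardised difference of 4.5/8.25 = 0.545 normally needs about 70 per group for 90% power at two-sided 5%, so 48 looks too small by about a third.

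This calculation is the stated basis for the size of the trial and concerns the primary outcome. If power at the MCID is about 75%, a real effect of that size would be missed about one time in four, not one in ten. The Introduction says the evidence could lead some centres to do fewer bronchoscopies, and the Discussion expects the results to enter guidelines. A non-significant result presented against a claimed 90% power would look like stronger evidence against benefit than it is.

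**Working it through.** **Inputs.** Difference 4.5, SD 8.25, alpha 0.05, power 90% and 48 evaluable per group (Sample size). Unpaired t-test with a 95% CI, hence two-sided 5% (statistical analyses section). Allocation 1:1 (Randomisation and allocation). For steps 1 to 5, 8.25 is taken as the SD of the quantity tested, which is the change score.

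**1. Trying to reproduce 48 per group.** With d = 4.5/8.25 = 0.545, the normal approximation is

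n per group = 2(z₀.₉₇₅ + z₀.₉₀)²/d² = 2(1.960 + 1.282)²/0.545² = 70.6, so 71.

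The noncentral t gives 71.6, so 72 per group or 144 evaluable. The printed 48 is not reproduced.

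**2. Power at the printed size.** The standard error of the difference is 8.25 × √(2/48) = 1.684. The noncentrality is 4.5/1.684 = 2.67.

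| Evaluable per group | Normal approximation | t-test |
|---|---|---|
| 48 | 76.2% | 75.3% |
| 57 (no dropout) | 82.9% | 82.3% |

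**3. Other readings that might give 48.**

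| Reading | Needed | Power at 48 per group |
|---|---|---|
| Two-sided 5%, 90% power | 72 per group | 75.3% |
| One-sided 5%, 90% power | 59 per group | 84.3% |
| Two-sided 5%, 80% power | 54 per group | 75.3% |
| One-sample or paired t-test, 90% power | 38 in total | not a comparison of groups |

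A one-sided 5% test with all 57 per group gives 89.4%. That is close to 90%, but the article ties 90% to 48 evaluable children and reports a 95% CI.

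**4. What would give 48 at 90%.** The t-test needs d = 0.6685. At SD 8.25 that is 0.6685 × 8.25 = 5.52 points, which is 23% above the MCID (5.52/4.5 = 1.23). At 4.5 points it is an SD of 4.5/0.6685 = 6.73. Neither figure is in the article.

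**5. Precision.** The expected 95% CI half-width at 48 per group is 1.986 × 1.684 = 3.34 points. An observed difference of 2 points would have an interval from about −1.3 to 5.3. It would be non-significant and still compatible with a benefit above 4.5.

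**6. If 8.25 is instead a single-visit SD.** The SD of change is 8.25 × √(2(1 − r)), where r is the T1–T2 correlation. The article gives no r, so these values are assumptions.

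| Assumed r | SD of change | t-test power at 48 per group |
|---|---|---|
| 0.3 | 9.76 | 61% |
| 0.5 | 8.25 | 75% |
| 0.6 | 7.38 | 84% |
| 0.67 | 6.70 | 90% |
| 0.7 | 6.39 | 93% |

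**7. Dropout.** 48/0.85 = 56.5, so 57 per group and 114 in all. This step is correct, and the fault lies only in the 48.

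**The case against.** The strongest objection is that 75% is conditional. The SD is printed beside the MCID with a citation and is not identified as an SD of change. If it is a single-visit SD and the sponsor assumed a T1–T2 correlation of about 0.67, then 48 per group does give 90%. The documents do not show whether the cause is an omitted correlation, a misprinted SD or a miscalculation. This stands as a limit on naming one true power. It does not rescue the sentence, because the correlation it needs is not stated and a correlation of 0.5 brings the power back to 75%.

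A second objection is that the article condenses a fuller protocol. That would answer a complaint about missing detail. Here the printed figures disagree with one another, and any assumption that reconciles them belongs beside them.

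A third is that recruitment was expected to end by late 2023, and that neither the estimate nor its CI depends on the power statement. This is true: the error does not bias the result, and the article already commits to a 95% CI. What remains is that a wrong power claim for the primary outcome would accompany the result and shape how a null finding is read.

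**Conclusion.** The concern holds. The article's own inputs do not yield 90% power with 48 children per group under any standard reading tried. With 8.25 as the SD of the change score and a two-sided 5% t-test, power is 75.3% at 48 per group and 82.3% at 57, and 90% would need 72 per group. The chance of missing a true 4.5-point effect is then about 25% at the planned evaluable size, against the 10% implied. If 8.25 is a single-visit SD, power at 48 runs from 61% to 93% for assumed correlations of 0.3 to 0.7 and reaches 90% only at about 0.67. The statement is therefore wrong as written. Because it is the design justification for the primary outcome, it must be corrected.

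**What to change.** 1. State whether 8.25 is the SD of the T2 minus T1 change or of a single score, and give any T1–T2 correlation used.
2. If it is the SD of change, replace the power statement with words such as: 48 evaluable children per group give about 75% power (82% with 57) for a 4.5-point difference with SD 8.25 at two-sided 5%; 90% power applies to a difference of 5.5 points. If it is a single-visit SD, print the correlation and the power that follows from it.
3. Keep N at 114.
4. Consider making the baseline-adjusted comparison the planned primary analysis rather than a fallback for imbalance. If 8.25 is the SD of change, the residual SD is 8.25 × √((1 + r)/2). At an assumed r of 0.5 this is 7.14 and power at 48 per group is 86%; at 0.6 it is 7.38 and 84%. This recovers part of the loss. The choice should be fixed before outcome data are compared by arm.
5. Interpret a non-significant result by whether the 95% CI excludes 4.5 points, not by the planned power.

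The cost is a rewritten sample-size paragraph and, if 8.25 is the SD of change, a less favourable power figure. Item 4 also changes the analysis text. No further children are needed.

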### Data management and statistical analyses and reporting

Essential study documentation and management of all study files are in accordance with good clinical practice guidelines. Further information about data management are provided in online supplemental file 1.

Data will be reported in accordance with Consolidated Standards of Reporting Trials, and ‘intention to treat’ (ITT) analyses will be used. For PedsQL 4.0, data will not be imputed, and ITT will consist of ‘available cases’. Based on our previous RCT,^38^ the change in PedQL 4.0 is expected to be normally distributed. The difference (with 95% CI) between groups of the change in QoL will be calculated using unpaired Student’s t-test. If the groups are imbalanced at baseline, regression analyses (adjusting for baseline factors) will be used instead. For the secondary outcomes of DASS21, STAI and PAC-QoL (including cough severity scores), the same method as per PedsQL 4.0 will be used. For the outcome of ‘change in management’, χ^2^ will be used to analyse the difference in the proportion between groups, presented as odds ratio (95% CI). Likert scales regarding opinions towards benefit of FB (parent and doctor perspective) will be reported as mean (SD) or median (25th–75th percentile), based on data distribution.

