### Endpoints

The primary endpoint is a change in QoL determined by the PedsQL 4.0 between the two arms at T2 (figure 1) (prior to control group having their FB) and the baseline (T1). The secondary endpoints are as follows: (a) proportion of children whereby FB changes clinical management based on a priori factors, (b) change in DASS21 scores (T2 minus T1), (c) change in PAC-QoL scores (including cough severity scores) (T2 minus T1), (d) change in STAI scores (T2 minus T1), (e) Likert scores reflecting opinions relating to the benefit of FB (patient and doctor perspective) in clinical practice and (f) change in PedsQL 4.0, DASS21, PAC-QoL (including cough severity score) or STAI in T4 and/or T5 (to examine if there is any sustained effect by the intervention (FB)).

A priori definitions of change in management are as follows:

Decision to admit for intravenous antibiotics and physiotherapy directly after FB. This will be based on the secretion score^29^ and the secretion colour which is part of a validated FB bronchitis score (Bscore)^37^ (see figure 2 for details of the management pathway). The importance of this management strategy in improving clinical outcomes has been previously highlighted by research findings.^38 39^
Started oral (PO) antibiotics directly after FB (excluding azithromycin for CT scan-proven BE). This will also be based on the secretion score,^29^ which is part of the Bscore^37^ (see figure 2 for details of the management pathway).Change in type of intravenous or PO antibiotics (or change from oral to intravenous) after BAL culture results are available(eg, anti-pseudomonal antibiotics for *Pseudomonas aeruginosa*).Referred to another specialty for appropriate management changes for intervention based on findings on FB. Examples include referral to surgeons such as cardiothoracic (eg, for vascular ring), ENT (eg, subglottic lesion) and paediatric (eg, tracheo-oesophageal fistula) surgeon.

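### The primary t-test on change gives way to regression only if the arms look imbalanced at baseline; one baseline-adjusted model should be fixed in advance

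*Protocol article*

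**What the plan says.** The Endpoints section defines the outcome as a change score: "The primary endpoint is a change in QoL determined by the PedsQL 4.0 between the two arms at T2", taken against T1. Under Data management and statistical analyses and reporting, the default analysis is unadjusted: "The difference (with 95% CI) between groups of the change in QoL will be calculated using unpaired Student’s t-test". The next sentence gives the exception: "If the groups are imbalanced at baseline, regression analyses (adjusting for baseline factors) will be used instead". For DASS21, STAI, PAC-QoL and cough severity, "the same method as per PedsQL 4.0 will be used", so the exception carries over to them.

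Under Randomisation and allocation, "Randomisation is stratified by as follows: (a) indication for FB", split into chronic cough and other, and also by age at a cut of 2 years. Neither factor enters the default analysis. No other section of the article sets an adjusted primary model.

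**The concern.** Allocation is concealed and randomised 1:1, so any baseline difference between arms is due to chance. The reason to adjust for a baseline variable is that it predicts the outcome, and that is known before the data arrive. Whether the arms happen to differ on it is a poor basis for choosing the model.

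Two things are at stake. First, the primary model is not settled until baseline data have been inspected, so two candidate primary results exist and a judgement about balance decides between them. Second, the default is the less precise of the two. A t-test on change forces a slope of 1 on the T1 score. When the true slope is below 1, it over-corrects any chance baseline difference, and it does so in the trials where imbalance was not judged large enough to trigger the switch.

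**Working it through.** **Inputs from the article (Sample size).** Difference 4.5; SD 8.25, with no statement whether this is the SD of a single score or of the change; α=0.05, taken here as two-sided; 48 evaluable children per group for 90% power.

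**Assumptions, not in the article.** T1–T2 correlation r, shown over a range; equal variance σ² at T1 and T2; normal data; adjustment for T1 PedsQL only. No strata effect is included.

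**The plan's own figure.** With 8.25 as the SD of the quantity tested, n = 2 × 8.25² × (1.960 + 1.282)² / 4.5² = 70.6, so 71 per group rather than 48. At 48 per group the t-test has 75% power (exact t). If 8.25 is instead the SD of a single score, the SD of change is 8.25 × √(2(1−r)). At r=0.66 that is 6.80, and 48 per group then gives about 89%. The sample size is a separate question and is used here only to set the scale.

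**Variance ratio.** Var(change) = 2(1−r)σ² and Var(ANCOVA) = (1−r²)σ². The ratio is (1−r²) / (2(1−r)) = (1+r)/2. At r = 0.3, 0.5, 0.7 and 0.8 this is 0.65, 0.75, 0.85 and 0.90.

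**Power at 48 per group, difference 4.5, two-sided 5%.** On the change reading the ANCOVA SD is 8.25 × √((1+r)/2). On the score reading the t-test SD is 8.25 × √(2(1−r)) and the ANCOVA SD is 8.25 × √(1−r²).

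| r | t-test (8.25 = SD of change) | ANCOVA (8.25 = SD of change) | t-test (8.25 = SD of score) | ANCOVA (8.25 = SD of score) |
|---|---|---|---|---|
| 0.3 | 75% | 91% | 61% | 79% |
| 0.5 | 75% | 86% | 75% | 86% |
| 0.7 | 75% | 82% | 93% | 96% |
| 0.8 | 75% | 80% | 99% | 99% |

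**The switch rule.** The article gives no trigger, so a baseline t-test at p<0.05 or p<0.20 was assumed. There were 40,000 simulated trials per setting, with 48 per arm and 8.25 as the SD of change. Results at r = 0.3 / 0.5 / 0.7:

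- Switch at p<0.05: type I error 4.0 / 4.2 / 4.5%; power 77 / 76 / 76%.
- Switch at p<0.20: type I error 3.2 / 3.7 / 4.2%; power 80 / 78 / 77%.
- ANCOVA always: type I error 4.9 to 5.1%; power 90 / 86 / 82%.
- t-test always: type I error 4.9 to 5.0%; power 75%.

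Switching at p<0.05 therefore recovers only a point or so of the available power, and at p<0.20 only part of it.

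**What an untriggered imbalance does.** Given a chance baseline difference D, the change-score estimate is off by (1−r)D. Take r=0.5, so that the single-score SD is also 8.25. A difference just short of p<0.05 is D = 1.985 × 8.25 × √(2/48) = 3.34 points. The estimate shifts by 0.5 × 3.34 = 1.67 points, which is 37% of the 4.5-point target. Such shifts average to zero over randomisations, so this is imprecision and not bias.

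**The case against.** The strongest defence is that an unpaired t-test on change is unbiased under randomisation, holds its nominal error rate and matches the endpoint as defined. That stands, and it limits the point to precision and pre-specification. Several stronger readings are tempting, and the article does not support them.

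- **Inflated type I error.** A reader might infer that having two candidate analyses inflates alpha. Reporting whichever of the two p-values is smaller would give 7.8 / 7.1 / 6.7% at r = 0.3 / 0.5 / 0.7. But the text ties the switch to balance at baseline, not to the results. Under the baseline triggers tested above, the procedure is conservative.
- **A trial already short of power.** This holds only if 8.25 is the SD of change. On the score reading, 48 per group gives about the stated 90% near r=0.66, and at r=0.7 ANCOVA adds only about 3 points.
- **Intervals too wide because the strata are ignored.** This follows only if age or indication predicts change in PedsQL. The article does not show that it does, and no size can be put on it.
- **Missing threshold and covariate list.** The article may leave these to the full protocol or analysis plan, neither of which is shown, so their absence is not the point. The conditional replacement of the primary model is stated in the article itself, and that is the point.

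**Conclusion.** The point holds as one of lost precision and an unfixed primary model. It should be fixed, but it does not threaten validity. The gain from a fixed ANCOVA depends on two things the article does not give: r, and which SD the 8.25 is.

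If it is the SD of change, power rises from 75% by about 16 points at r=0.3, 11 at r=0.5, 7 at r=0.7 and 5 at r=0.8. If it is the SD of a single score, the gain is about 18, 11 and 3 points at r = 0.3, 0.5 and 0.7. These figures assume equal T1 and T2 variances and credit nothing to the strata. For any r below 1 the fixed model is the more precise of the two, apart from the negligible cost of estimating the slope.

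**What to change.** By a dated amendment made before any outcome comparison by arm:

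1. Make the single primary analysis a linear model of T2 parent-proxy PedsQL total on arm, T1 parent-proxy PedsQL total, age stratum and indication stratum. Report the adjusted difference with its 95% CI whatever the baseline balance.
2. Delete the sentence that brings in regression only on imbalance.
3. Keep the unadjusted t-test on change as a sensitivity analysis.
4. Use the same model for DASS21 and STAI, each with its own T1 score.
5. For PAC-QoL and cough severity, adjust for the T1 score and age stratum only. The overview of procedures collects these where cough is the indication, while Table 1 says where cough is present. In that subset the indication term is constant or nearly so.

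No new data are needed, because the T1 scores and both strata are already recorded. The cost is in timing and documentation. Recruitment began in May 2020 and was due to end by late 2023, and the article appeared in February 2024. Much of the data may already be held and physicians are not blinded, so the amendment should state its date and that no outcome had been compared by arm.

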### Further description of data collection

Data are collected from parent interview and from medical records. At baseline, demographic data, medical history, medications, tobacco smoke exposure, birth history and spirometry (if available) are recorded. The treating respiratory paediatrician undertaking the FB documents the child’s provisional expected FB findings and overall clinical diagnosis, indication for FB and proposed investigations and therapy before the FB at baseline (T1). Routine respiratory examination is also collected using standardised data collection sheets (eg, cough pointers; digital clubbing; chest wall deformity; ear, nose and throat; and auscultation). On the day of the FB, parents are asked to rate their child’s cough using validated score^27^ (which is repeated in the post-FB clinic follow-up appointment), if cough is present. After the FB has been undertaken, the treating physician documents the following:

The FB and overall clinical diagnosisWhether FB leads to confirmation or exclusion of provisional diagnosisIf there is a new diagnosis and if confirmation of provisional FB diagnosis changed managementIf exclusion of provisional FB diagnosis has reassured the clinician and/or family and/or changed existing management

The a priori definition of change in management (defined below) is documented after FB. The CT of the chest (if one is done concurrently, ie under the same general anaesthetic as the FB) diagnosis is also recorded, and if any management was new or changed due to the CT result is also recorded so as not to have this as a confounding variable. The physician fills in three 10-point Likert point questionnaires (1=not at all, 10=very much) regarding the FB contribution to diagnostic clarity, therapeutic management and education or counselling of parent(s) (how much did the FB contribute to the diagnostic clarity in this case, how much did the FB increase confidence in the therapeutic management of the child and how much did the FB aid in educating/counselling the parent/guardian). Complications occurring during the FB procedure are also collected including laryngospasm, bronchospasm, nasal trauma/epistaxis (for transnasal approach), pneumothorax, pulmonary haemorrhage and/or if there is hypoxia which necessitates the removal of bronchoscope for bag-mask ventilation or intubation. The SpO2 nadir will also be recorded in this instance.

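### The between-arm χ² test and odds ratio for change in management cannot show whether FB changes management, and the stated 95% power matches neither comparator the design implies

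*Protocol article*

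**What the plan says.** **Endpoint.** The Endpoints section lists secondary endpoint (a) as the "proportion of children whereby FB changes clinical management based on a priori factors". Unlike endpoints (b) to (d), which are T2 minus T1, it carries no timepoint.

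**Definitions.** The same section gives four qualifying events: admission for intravenous antibiotics and physiotherapy straight after FB; oral antibiotics begun straight after FB; a switch of antibiotic once lavage cultures are back; and referral to another specialty because of what FB showed.

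**Recording.** Further description of data collection states: "The a priori definition of change in management (defined below) is documented after FB".

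**Schedule.** Table 1 gives the early arm its FB 1–2 weeks after baseline and the controls theirs at T3, at least 6 weeks after baseline. The physician's opinion on diagnosis and management is scheduled for controls at T1, T3 and T3+2–3 weeks, but not at T2.

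**Analysis.** The statistical section says a χ² test "will be used to analyse the difference in the proportion between groups, presented as odds ratio (95% CI".

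**Power.** The Sample size section says that "the effect size is conservatively estimated based on pilot data of a random selection of 20 FBs", reports a change in 14 of 20 (70%), and concludes: "The sample size of 114 provides 95% power (α=0.05) for this outcome (taking into account 15% loss". It gives no second proportion.

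**The concern.** The first secondary aim asks whether FB leads to a change in management. A test between randomised arms can answer that only if the outcome could occur in a child who has not had FB. Here it cannot, because each qualifying event is defined by reference to the procedure or its lavage result.

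The result then depends on a timepoint the article does not state. One choice makes a significant difference a product of the definitions. The other compares two groups that have both had FB. A p-value from the first could be presented as randomised evidence that FB alters care. A null result from the second could be misread as evidence that it does not. The outcome also has its own power claim, which lends the comparison a weight it cannot carry.

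**Working it through.** **Inputs.** Pilot rate p₁ = 14/20 = 0.70 (Sample size). Enrolment is 57 per arm with 15% loss, so 57 × 0.85 ≈ 48 evaluable per arm, and the primary calculation also uses 48. α = 0.05. Sidedness is not stated; two-sided is assumed and one-sided also tried. The comparator p₂ is not stated and was varied from 0 to 0.70.

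**Step 1: does each definition need an FB?**

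| Qualifying event | What it depends on |
|---|---|
| Admission for intravenous antibiotics and physiotherapy | timing after FB, secretion findings |
| Oral antibiotics started | timing after FB, secretion findings |
| Antibiotic changed | lavage culture, taken at FB |
| Specialty referral | FB findings |

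All four do. A control who needs an urgent FB before T3 meets an exit criterion, so that route does not supply control events either.

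**Step 2: test at T2.** Controls are 0/48 by definition. With k events among 48 early-arm children, the uncorrected statistic is

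χ² = 96·(48k)² / [48·48·k·(96−k)] = 96k/(96−k).

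- k = 3: 288/93 = 3.10, below 3.84.
- k = 4: 384/92 = 4.17, above 3.84.
- k = 34 (about 70%): 3264/62 = 52.6.

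So 4 of 48 (8%) is enough for significance. The sample odds ratio has a zero in its denominator and is infinite. Power at 70% vs 0% is 1.00.

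**Step 3: test after each child's own FB.** Both arms have had the same procedure and follow the same standard of care. If waiting has no effect, the comparison is 70% vs 70%, and exact enumeration of the χ² test with 48 per arm rejects 5.2% of the time, which is the type I error. Any real difference would reflect the effect of the wait.

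**Step 4: try to reproduce the 95% power.** The pooled-variance formula is

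power = Φ{ [ |p₁−p₂| − 1.96·√(2p̄(1−p̄)/n) ] / √[ (p₁(1−p₁) + p₂(1−p₂))/n ] }, with p̄ = (p₁+p₂)/2.

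For p₂ = 0.34 and n = 48, p̄ = 0.52. The first root is √(0.4992/48) = 0.1020, and 1.96 × 0.1020 = 0.1999. The denominator is √(0.4344/48) = 0.0951. Power = Φ[(0.36 − 0.1999)/0.0951] = Φ(1.68) = 0.954. Exact enumeration also gives 0.954.

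| Comparator p₂ | Power, 48 per arm, two-sided |
|---|---|
| 0% | 1.00 |
| 30% | 0.98 |
| 34% | 0.95 |
| 40% | 0.85 |
| 50% | 0.52 |
| 60% | 0.17 |

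The comparator giving 95% is therefore about 34%. Changing one convention at a time gives about 32% (continuity correction), 37% (one-sided) or 37% (all 57 per arm). One-sided with 57 per arm gives 40%. None is close to 0% or 70%.

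A one-sample test of 70% against 50% does not recover 95% either: it gives 81% (n = 48), 88% (n = 57), 98% (n = 96) and 99% (n = 114).

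**Step 5: precision of a pooled proportion.** For 67/96 = 0.698, the Wilson centre is (0.698 + 3.84/192)/(1 + 3.84/96) = 0.690. The half-width is 1.96·√(0.698 × 0.302/96 + 3.84/(4 × 96²))/1.04 = 0.090. The interval is 60.0% to 78.1%.

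**The case against.** Four points can fairly be made for the plan.

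- **The aim can still be met.** Endpoint (a) is worded as a single proportion, and its data are collected after FB in both arms. This stands. A reader might infer that the trial cannot address its first secondary aim; the documents do not support that. The fault lies in the χ²/odds-ratio sentence and the power sentence.
- **A post-FB comparison has a legitimate meaning.** Controls wait at least 6 weeks, and disease may evolve or resolve meanwhile. This also stands. A reader might infer that the arms must be equal after FB, so that a null result is guaranteed; that assumes waiting has no effect. What can be said is that the comparison estimates an effect of timing, which is a different question.
- **The comparator may be given in a fuller document.** The article is condensed, so an unstated control rate is not in itself a defect. The objection to the power figure is that the rate it needs fits neither situation the definitions allow.
- **The planners call their estimate conservative.** The pilot's exact 95% interval is 46–88%, and a reader might take that as disproving the word. It shows imprecision only. The text does not say what effect size was used, so the description can be neither confirmed nor refuted.

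**Conclusion.** The point holds as a correction to a secondary analysis. As defined and recorded, change in management cannot occur without FB, so a between-arm test is either settled by definition (0% in controls at T2) or tests the timing of FB. Neither tells the reader whether FB changes management.

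The 95% power needs a comparator of about 34%, or 32–37% when one convention is varied at a time, and neither 0% nor about 70% is compatible with it. This assumes a two-proportion test with about 48 evaluable children per arm and the pilot rate of 70% in the early arm. The value of about 70% for controls after FB further assumes little effect of waiting.

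The primary endpoint (PedsQL change, T2 minus T1) is untouched. The target of 114 was derived from that endpoint and does not rest on this power claim.

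**What to change.** 1. **Replace the χ² test and odds ratio** with the proportion of all children who had FB, arms pooled, whose management changed, with a Wilson 95% CI. This follows endpoint (a) as worded and needs no new data.
2. **Replace the 95% power statement** with expected precision: if about 70% of 96 children have a change, the 95% CI runs from about 60% to 78%.
3. **Optional.** If a randomised comparison is wanted, define management change between T1 and T2 without reference to FB, and abstract it identically in both arms from the chart review that Table 1 schedules for both at T2. Label it as added late, since recruitment was expected to finish by late 2023. State that only the early arm has a clinical assessment and post-baseline physician opinion by T2, so ascertainment is unequal and may favour FB.

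Items 1 and 2 cost a few sentences, plus the loss of a p-value and a power figure that carry no information about the aim. Item 3 costs extra abstraction and a caveat in the report, and should be left out if the ascertainment problem is judged too large.
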